### Statistical analysis

Data will be analyzed according to the intention-to-treat principle. Differences in continuous outcomes will be tested using independent samples t-tests or nonparametric equivalents, depending on the distribution. Chi squared tests (or Fishers Exact tests) will be used to test differences in categorical variables. Adjusted analyses will be performed in case of unbalanced randomization between the intervention and control arm. A *P* value of 0.05 is considered significant. Statistical analyses will be performed using Statistical Package for Social Sciences (SPSS) software (IBM SPSS Statistics for Windows, Armonk, NY: IBM Corp.).

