### Random selection

Participants who meet the inclusion criteria of the SPONGE trial form a subcohort of eligible patients (Fig. 1). From this subcohort, patients are randomly selected on a 1:1 basis. Randomly selected patients are offered sponge-assisted surgery. Stratified randomization is performed to take into account participation in other ongoing trials within the cohort, of which the (secondary) endpoints may interfere with endpoints of the SPONGE trial. At this moment, patients are stratified according to whether they received boost radiotherapy in the context of the RECTAL BOOST study, which is running as a cmRCT within the cohort (ClinicalTrials.gov: NCT01951521) [14]. In this trial, a randomly selected group of patients with locally advanced rectal cancer is offered an additional radiation boost prior to standard neoadjuvant chemoradiation. Stratified randomization, using dedicated software, takes place at the Imaging Division University Medical Center Utrecht.

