### Data collection

Clinical data are being captured from the patients’ electronic medical files and will be collected in an electronic database encompassing data of all cohort participants. In this database, variables are registered under a unique study number provided to each cohort participant. For patients in the SPONGE trial, additional clinical information, that is, duration of surgery, blood loss, fluid balance, postoperative body temperature, and oxygen therapy, will be collected from electronic medical files. Only the research office of the Imaging Division, University Medical Center Utrecht, possesses the key to link study numbers back to patient identifiers. At baseline, data will be collected on demographics, body mass index, co-morbidities, tumor characteristics, neoadjuvant therapy, ASA classification, type of anesthesia, and surgical procedure.

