This trial is relevant because the number of (non-)surgical postoperative complications after colorectal surgery is substantial and result in a relatively high morbidity and mortality rate [19, 20]. Even though laparoscopic colorectal surgery is associated with certain benefits as a shorter hospital stay, less blood loss, and a faster recovery of bowel function, the risk on postoperative cardiopulmonary complications is not evidently lower than in open surgical procedure. A systematic review on nonsurgical complications following laparoscopic or open surgery for colorectal cancer showed no difference in the risk of pulmonary complications (pooled analysis for laparoscopy in colon cancer (OR 0.78, 95 % CI 0.53 to 1.13) and in rectal cancer (OR 1.19, 95 % CI 0.74 to 1.90)) [21]. Significantly fewer cardiac adverse events were observed in patients undergoing colectomy, but not in those undergoing rectal surgery (OR 0.28, 95 % CI 0.11 to 0.71 and OR 0.85, 95 % CI 0.41 to 1.71, respectively). This could be a result of the more extensive surgery, longer operation time, and higher risk on overall postoperative morbidity in rectal surgery [22]. Several studies presented the effects of the Trendelenburg position on perioperative cardiopulmonary parameters, but postoperative data are lacking [7, 8, 23–26]. Besides, the effect of a patient’s position as an independent factor is hard to evaluate because the perioperative hemodynamic parameters are partly influenced by pneumoperitoneum, which is the CO_2_ gas insufflation in the abdominal cavity [3].

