A challenging aspect of the cmRCT design is the fact that multiple trials are conducted simultaneously within one cohort. In patients eligible for multiple trials, interference of endpoints between trials might occur. As mentioned earlier, some of the patients eligible for the SPONGE trial will have participated in the RECTAL BOOST study [14]. Patients having received the boost intervention potentially have a higher risk on acute toxicity than patients who undergo standard chemoradiation [30], which could result in perioperative complications and thereby prolonged hospital stay. In order to balance the number of patients treated with the experimental boost intervention between both arms, stratified randomization is required. The main advantage of stratified randomization is the systematic balance of factors, which may influence outcome measures between treatment groups resulting in trial efficiency, increased power and less need for (biased) post-hoc analysis [31]. Furthermore, stratified randomization enables the possibility to detect potential interactions between the boost intervention and outcome measures of the SPONGE trial. On the other hand, the more trials conducted within one cohort, the more strata required for randomization in every new trial. This will result in complex trial coordination, treatment allocation, and trial administration. Having too much trial-induced strata may result in overstratification. This could lead to unfilled strata, unequal distribution of stratification factors, or the need for adjusted analysis [31–33]. In addition, it is yet unclear if there is such as a limit in number of interventions per patient within the cmRCT design. In our cohort, these new methodological challenges should be taken into account when a new trial is initiated. In the future, expertise of clinicians will be essential in the design of new cmRCT-based trials because overlap of endpoints must be considered in an early stage since this could affect potential recruitment rates and thereby the succeeding of a trial.

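### Hospital stay is tested without the randomisation stratum and adjusted only if the arms look unbalanced, with no statement of which result is then primary

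*Protocol article*

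**What the plan says.** All places are in the protocol article.

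- **Statistical analysis.** "Differences in continuous outcomes will be tested using independent samples t-tests or nonparametric equivalents, depending on the distribution". This covers the primary endpoint, days from surgery to discharge. The rule on covariates is "Adjusted analyses will be performed in case of unbalanced randomization between the intervention and control arm". The section does not say whether an adjusted result would replace the unadjusted one or stand beside it.
- **Random selection.** "At this moment, patients are stratified according to whether they received boost radiotherapy in the context of the RECTAL BOOST study".
- **Discussion, on the boost.** Its possible acute toxicity is something "which could result in perioperative complications and thereby prolonged hospital stay". The design therefore treats the stratum as potentially prognostic for the primary endpoint.
- **Discussion, on why to stratify.** The benefit is described as balance "resulting in trial efficiency, increased power and less need for (biased) post-hoc analysis".
- **Blinding.** Investigators and physicians know the allocation.

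**The concern.** Stratifying the randomisation on a prognostic factor yields its gain in power only if the analysis also uses that factor. In an unstratified two-sample test, the standard error still contains the variation between strata. A rule triggered by imbalance does not repair this: successful stratification balances the boost factor, so the trigger will seldom select it.

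The rule also makes the analysis depend on the data. If some baseline factor differs between arms, there will be an unadjusted and an adjusted result for hospital stay, and the text does not say which one decides the trial. People who know the allocation could settle that after seeing both. This is the post-hoc step that the Discussion says stratification should make less necessary.

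At stake are some precision and protection against a selected result, not the validity of the basic comparison.

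**Working it through.** **Inputs from the protocol (Sample size).** SD 2.04 days; difference 1 day; refusal 10% in the intervention arm; two-sided alpha 5%; power 80%; final size 98 per arm.

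**Step 1. Reproduce the plan's figure.** Without refusal, 2 × (1.96 + 0.842)² × 2.04² / 1² gives 66 per arm. Refusers receive standard surgery, so the intention-to-treat difference is 1 × 0.9 = 0.9 day. Then 66 / 0.9² = 81.5, that is 82; solving the t-test directly gives 81.6, also 82. The stated 82 is reproduced.

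**Step 2. Power of the unadjusted test.** At 98 per arm the standard error is 2.04 × √(2/98) = 0.2914, and 0.9 / 0.2914 = 3.088. Power = Φ(3.088 − 1.96) = 87.0%. Dividing 98 by 1.15, to undo the plan's 15% addition for nonparametric testing, gives 82.1%. With the Abstract's 94 per arm the two figures are 85.6% and 80.5%. All are above 80%.

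**Step 3. Gain from the boost stratum alone.** The documents give neither its prevalence *p* nor its effect *s* on stay, so both are assumed. R² = p(1 − p)s² / 2.04². Under balanced stratification:
- true alpha of the unadjusted test = 2 × [1 − Φ(1.96 / √(1 − R²))]
- power unadjusted = Φ((3.088 − 1.96) / √(1 − R²))
- power adjusted = Φ(3.088 / √(1 − R²) − 1.96)

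| p | s (days) | R² | True alpha, unadjusted | Power unadjusted | Power adjusted |
|---|---|---|---|---|---|
| 0.05 | 1 | 0.011 | 0.049 | 87.2% | 87.4% |
| 0.05 | 2 | 0.046 | 0.045 | 87.6% | 88.5% |
| 0.10 | 1 | 0.022 | 0.048 | 87.3% | 87.7% |
| 0.10 | 2 | 0.087 | 0.040 | 88.1% | 89.8% |
| 0.20 | 1 | 0.038 | 0.046 | 87.5% | 88.3% |
| 0.20 | 2 | 0.154 | 0.033 | 89.0% | 91.9% |

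The gain is 0.2 to 2.9 points, and leaving the stratum out makes the test conservative. At the extreme of s = 3 days and p = 0.20 (R² 0.346) the gain would be 5 points (91.9% to 96.9%).

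**Step 4. Gain from prognostic covariates fixed in advance.** R² is again an assumption. Power = Φ(3.088 / √(1 − R²) − 1.96) at 98 per arm:

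| R² | 98 per arm | 98 / 1.15 per arm |
|---|---|---|
| 0 | 87.0% | 82.1% |
| 0.02 | 87.7% | 82.9% |
| 0.05 | 88.7% | 84.0% |
| 0.10 | 90.2% | 85.9% |
| 0.20 | 93.2% | 89.6% |
| 0.30 | 95.8% | 93.1% |

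These are linear-model figures and only a guide to a rank test.

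**Step 5. The imbalance rule itself.** The Data collection section lists eight groups of baseline factors. If they are treated as eight independent factors tested at p < 0.05, the chance that at least one is flagged under correct randomisation is 1 − 0.95⁸ = 33.7%. A simulation (10,000 trials per setting, 98 per arm, eight independent normal covariates, total R² 0.10 to 0.30) gave:

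| Analysis | Type I error | Power at 0.9 day |
|---|---|---|
| Unadjusted | 4.7–5.0% | about 87% |
| Adjust only for flagged factors | 4.2–4.8% | about 87% |
| All eight covariates, fixed in advance | 4.9–5.0% | 89–95% |
| Better of unadjusted and triggered | 5.2–5.5% | 88–89% |
| Better of unadjusted and fully adjusted | 6.6–7.6% | 91–96% |

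The simulation error near 5% is about √(0.05 × 0.95 / 10,000) = 0.2 points. The triggered rule recovers almost no precision. Error rises only when the better of two results is reported.

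**The case against.** The strongest reply is that model terms and covariate lists belong in an analysis plan that is not shown. That holds for the covariate list and for a threshold for imbalance. It does not hold for the rule: the article states that adjustment is conditional, and a plan that adjusted whatever the balance would contradict it.

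A second reply is that the Discussion links unequal distribution of stratification factors to a need for adjusted analysis, so the trigger may mean failed stratification only. That reading is possible. Even then the stratum enters the analysis only when stratification has failed, whereas the power gain needs it there when stratification has worked.

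Third, baseline balance can be judged without outcome data, and the unadjusted tests are named first. Both are true, and a mechanically applied rule does no harm to the error rate. The text still does not commit to the unadjusted result as primary.

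Some stronger readings are tempting but not supported:

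- *That the test is invalid or the trial underpowered.* Steps 2, 3 and 5 show otherwise on the stated SD.
- *That chance imbalance in tumour site could seriously distort the estimate.* If half the patients had rectal cancer and stayed 2 days longer, a 14-point imbalance (1.96 × √(2 × 0.25/98) = 0.14) would shift the estimate by 0.14 × 2 = 0.28 day. Neither assumption is in the documents. A split of 56/98 against 42/98 has p of about 0.046 and would probably trigger the plan's own adjustment. Chance imbalance is also already reflected in the unadjusted standard error.
- *That tumour site is the main predictor of stay.* The Discussion refers to "more extensive surgery, longer operation time, and higher risk on overall postoperative morbidity in rectal surgery" only as a possible explanation of differing cardiac results between laparoscopic and open surgery. It does not compare stay between sigmoid and rectal cancer.
- *That the trial will adjust for factors settled after allocation.* "ASA classification, type of anesthesia, and surgical procedure" are listed as baseline data. Nothing says that they are decided after random selection or will be used as covariates.

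**Conclusion.** The point holds in a limited form. The article fixes unstratified tests and imbalance-triggered adjustment without naming the primary result. This sits badly with its own reasons for stratifying, and it leaves a choice between results open in an open-label trial.

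The cost is lost efficiency and an avoidable freedom of choice. For the boost stratum alone the loss is about 0 to 3 power points, assuming 5–20% prevalence and a 1–2 day effect. For tumour site or other prognostic factors it depends on an R² that the documents do not give: 0.10 to 0.30 would move power from about 87% to 90–96% at 98 per arm, and smaller values would move it less. Type I error is at risk only if the more favourable result is chosen, reaching at most about 7.6% in the settings simulated. This is a worthwhile improvement to the plan, not a threat to its validity.

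**What to change.** Replace the sentence on adjusted analyses with one fixed primary analysis. For example:

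*Hospital stay is compared between the randomised arms with a van Elteren test stratified by the randomisation stratum (boost yes/no) and tumour site (sigmoid/rectum), whatever the observed balance. The unstratified two-sample test is a sensitivity analysis. Any further covariate is limited to values fixed before random selection.*

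The stratification has three cells, not four, because the boost is given only in rectal cancer: sigmoid, rectum without boost, rectum with boost. A rank-based test also suits the plan's expectation that stay is not Gaussian.

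The cost is one sentence in the protocol and analysis plan. The stratum is known from randomisation, and tumour site is part of the eligibility criteria. The team should confirm that SPSS, the software named, can run the test, or name a package that can. Because the trial is already enrolling, the change should be dated and made before anyone looks at outcomes by arm.

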### Safety reporting

Within the observational colorectal cancer cohort, serious adverse events (SAEs) are measured by an annual questionnaire. For the present study, serious adverse device events (SADEs) and study-specific SAEs are measured, including major complications, as an event within the first 30 days after sponge-assisted surgery resulting in any serious surgical complications or any medical event resulting in death or a life threatening situation. The sponsor will report these events within 15 days after notification. SADEs that result in death or are life threatening are reported within 7 days after the responsible investigator has first knowledge of it. SADEs and SAEs are reported on a Dutch web portal (www.toetsingonline.nl).

## Discussion

The SPONGE trial is the first randomized controlled trial to evaluate the impact of the use of the retractor sponge during laparoscopic colorectal surgery on duration of hospital stay and postoperative complications. Since no alternative for the Trendelenburg position has been available, the clinical relevance of the effects related to this position has never been investigated. Recently, results of a pilot study suggested that avoidance of the Trendelenburg position might reduce the postoperative hospital stay [10]. This effect could potentially be explained by a more stable perioperative hemodynamic status, which may make patients less prone to develop complications. Since this pilot study was a nonrandomized retrospective matched analysis, the risk of bias is considerable. Therefore, a randomized trial is warranted to estimate an unbiased effect of the Trendelenburg position on postoperative complications and hospital stay.

This trial is relevant because the number of (non-)surgical postoperative complications after colorectal surgery is substantial and result in a relatively high morbidity and mortality rate [19, 20]. Even though laparoscopic colorectal surgery is associated with certain benefits as a shorter hospital stay, less blood loss, and a faster recovery of bowel function, the risk on postoperative cardiopulmonary complications is not evidently lower than in open surgical procedure. A systematic review on nonsurgical complications following laparoscopic or open surgery for colorectal cancer showed no difference in the risk of pulmonary complications (pooled analysis for laparoscopy in colon cancer (OR 0.78, 95 % CI 0.53 to 1.13) and in rectal cancer (OR 1.19, 95 % CI 0.74 to 1.90)) [21]. Significantly fewer cardiac adverse events were observed in patients undergoing colectomy, but not in those undergoing rectal surgery (OR 0.28, 95 % CI 0.11 to 0.71 and OR 0.85, 95 % CI 0.41 to 1.71, respectively). This could be a result of the more extensive surgery, longer operation time, and higher risk on overall postoperative morbidity in rectal surgery [22]. Several studies presented the effects of the Trendelenburg position on perioperative cardiopulmonary parameters, but postoperative data are lacking [7, 8, 23–26]. Besides, the effect of a patient’s position as an independent factor is hard to evaluate because the perioperative hemodynamic parameters are partly influenced by pneumoperitoneum, which is the CO_2_ gas insufflation in the abdominal cavity [3].

The retractor sponge may provide two additional advantages. In the Trendelenburg position, cephalad excursion (sliding) of the patient while on the operation table can be problematic, particularly for obese patients or when the tables are positioned at steep angles. Sliding can cause skin and neuropathic injuries and can disturb the surgical procedure [27, 28]. Some devices used for sliding prevention, such as shoulder braces or headrests, can induce neuromuscular injuries, particularly brachial plexus injury, and are therefore not recommended [27]. In sponge-assisted surgery, patients are operated in horizontal position with no risk of sliding. Another potential benefit of a horizontal position is a more comfortable ergonomic position for the surgeon. The retractor sponge allows the surgeon to work with laparoscopic instruments in a horizontal line with the patient, which may reduce tension in the arms and neck. Unfortunately, we are not able to investigate these potential ergonomic benefits because this trial is performed at only one center with extensive experience in sponge-assisted surgery.

This study uses the cmRCT design. This design aims to overcome shortcomings of classic RCTs such as slow recruitment, disappointment bias in patients randomized to the control arm, and poor generalizability due to enrollment of only a small proportion of eligible patients [14, 29]. Trial recruitment within the PLCRC cohort is expected to be more efficient because patients are recruited from a large patient cohort, and only patients randomly selected for the intervention are informed about the intervention. In popular low risk interventions, such as the one used in the present study, the risk of disappointment bias or dropout in the control arm, due to a strong preference for the sponge intervention, is therefore diminished.

A challenging aspect of the cmRCT design is the fact that multiple trials are conducted simultaneously within one cohort. In patients eligible for multiple trials, interference of endpoints between trials might occur. As mentioned earlier, some of the patients eligible for the SPONGE trial will have participated in the RECTAL BOOST study [14]. Patients having received the boost intervention potentially have a higher risk on acute toxicity than patients who undergo standard chemoradiation [30], which could result in perioperative complications and thereby prolonged hospital stay. In order to balance the number of patients treated with the experimental boost intervention between both arms, stratified randomization is required. The main advantage of stratified randomization is the systematic balance of factors, which may influence outcome measures between treatment groups resulting in trial efficiency, increased power and less need for (biased) post-hoc analysis [31]. Furthermore, stratified randomization enables the possibility to detect potential interactions between the boost intervention and outcome measures of the SPONGE trial. On the other hand, the more trials conducted within one cohort, the more strata required for randomization in every new trial. This will result in complex trial coordination, treatment allocation, and trial administration. Having too much trial-induced strata may result in overstratification. This could lead to unfilled strata, unequal distribution of stratification factors, or the need for adjusted analysis [31–33]. In addition, it is yet unclear if there is such as a limit in number of interventions per patient within the cmRCT design. In our cohort, these new methodological challenges should be taken into account when a new trial is initiated. In the future, expertise of clinicians will be essential in the design of new cmRCT-based trials because overlap of endpoints must be considered in an early stage since this could affect potential recruitment rates and thereby the succeeding of a trial.

A limitation of this study is that the trial is performed in a single center by a surgeon experienced with sponges. In the near future, other centers may participate, which will enhance the generalizability of the results. In addition, the trial is performed unblinded. The pragmatic cmRCT design makes blinding impossible because information must be provided to randomly selected patients because they have to choose whether they want to undergo sponge-assisted or standard surgery. Clinicians cannot be blinded because perioperative use of the sponge must be reported in the operation report for safety reasons. To minimize observer bias in physicians responsible for discharge of the patients, we use an objective primary endpoint in the form of a discharge checklist. Both intervention arm and control patients will be assessed by this checklist provided to attending physicians. According to the cmRCT design, patients in the control arm are not aware of the fact that a sponge intervention is available, which may minimize disappointment bias.

In conclusion, this trial will evaluate the clinical effects of sponge-assisted laparoscopic colorectal surgery compared to the standard Trendelenburg positioning. Results of the trial will be applicable to other institutions performing laparoscopic colorectal surgery, as well as to other laparoscopic pelvic procedures that make use of the Trendelenburg position.

